## Methods and analysis

### Objectives and study design

The TaiChi-MSS study is a randomized, controlled, single-blind trial conducted across multiple centers in Suzhou and Shanghai, in which the outcome assessors will be blinded to group assignments. Block randomization, with a fixed block size of four, will be used to allocate enrolled participants into one of four arms, ensuring balanced group allocation. A total of 22 participants will be assigned to each arm, with random allocation to the Tai Chi group (TCG), the Tai Chi combined with multisensory stimulation group (TMCSSG), the control group (CG), or the multisensory stimulation group (MSSG) according to a 1:1:1:1 allocation ratio. Outcome assessors will be masked to allocate and will not be involved in the interventions. Primary outcomes include assessing changes in cognitive function—such as attention, memory, language, visuospatial ability, and executive function—after a 24 weeks intervention period. Secondary outcomes involve evaluating sensory function through air conduction, pure tone hearing thresholds, and olfactory recognition levels, as well as analyzing the correlation between hippocampal subregion atrophy rates and volumes of auditory and olfactory regions using structural MRI.

As illustrated in Figure 1, this study will be conducted in three phases. Phase 1 is the development of the intervention, and Phase 2 comprises the screening, baseline assessment, and randomization of the participants and the execution of the multidomain intervention. Phase 3 is the approach modeling.

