### Intervention program

A factorial experimental design with four factors 4 × 4 will be used. All participants will be randomly assigned to one of the four groups: control group (CG), Tai Chi group (TCG), multisensory stimulation group (MSSG), or Tai Chi combined with multisensory stimulation group (TCMSSG). Key characteristics will be stratified; the stratification factors considered in this study include sex, years of education, and age to ensure that the groups are balanced.

The intervention will last for 6 months, followed by assessments at baseline, 3, 6, and 9 months. These assessments will include changes in overall cognitive function, measured through attention, memory, language, visuospatial ability, and executive function. Sensory function will be evaluated using air conduction, pure tone hearing threshold, and olfactory recognition tests. Functional MRI (fMRI) will be utilized to evaluate neural network connectivity and the effectiveness of the intervention on brain function.

The intervention for the Tai Chi groups (TCG and TCMSSG) will be based on exercise recommendations for older adults from the American College of Sports Medicine (ACSM). The 6 months intervention will include three weekly sessions, each lasting 50 min. The target heart rate (THR) will be calculated using the reserve heart rate percentage method (Table 2):

**TABLE 2 T2:** Exercise intensity intervention program [Tai Chi group (TCG) and Tai Chi combined with multisensory stimulation group (TCMSSG)].

Elements of intervention	Initial stage (4 weeks)	Mid-term (10 weeks)	Late stage (10 weeks)
Intensity of exercise	45% 55% HRmax	55% 65% HRmax	65% 75% HRmax
Frequency of movement	3 times a week	3 times a week	3 times a week
Duration	40 60 min	50 70 min	50 70 min

THR=(HRmax-HRrest)×intensity⁢(45%-75%)+

HRrest⁢(Lindenberger, 2008).

Additionally, the Borg Rating of Perceived Exertion (RPE) scale will be used to monitor participants’ subjective fatigue levels during the sessions.

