### Statistical analysis

Statistical Package for Social Sciences (SPSS) software (version 23.0) will be used for statistical analysis. An alpha level of (0.05) will be considered for all statistical tests. Two-sided *P*-values of (0.05) and (80%) power indicate statistical significance (Schulz et al., 2010). A mixed effect model will analyze the results and be employed for statistical analysis of the variance of the pretest (baseline score) and posttest (3, 6, 9 months) in the four groups. All mental, cognitive, sensory, and physical outcome measures will be used for statistical analysis. Discovery Rate (FDR) correction will be used for *post hoc* analysis.

Given the variety of cognitive and fMRI outcome measures, we will apply the False FDR to control for multiple comparisons (Genovese et al., 2002). Bonferroni correction will be used only if necessary for specific hypotheses with fewer comparisons, but FDR will be the primary approach (Alspach, 1996). An intention-to-treat (ITT) approach will be employed to handle missing data (Gupta, 2011; Little, 2024). Multiple imputations will be applied for missing cognitive data. Participants with incomplete or poor-quality fMRI data, such as those affected by motion artifacts, will be excluded from the fMRI analysis but kept in the cognitive analysis. Specific handling of missing data will depend on the outcome type.

Functional MRI (fMRI) will be utilized to evaluate neural network connectivity and the effectiveness of the intervention on brain function. Pearson correlation analysis will be conducted to assess the relationship between hippocampal subregion atrophy and the volumes of auditory and olfactory regions using structural MRI data. Similarly, Pearson or Spearman correlation coefficients will be calculated, depending on the distribution of the data, to explore the associations between fMRI-derived connectivity metrics and cognitive and sensory outcomes. These analyses aim to uncover potential neural mechanisms underlying the effects of the interventions. A sensitivity analysis will be performed by varying hypothetical dropout rates and effect sizes to assess their impact on the statistical power and required sample size (Little, 2024).

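### The correlations meant to show neural mechanisms are named as simple coefficients, which cannot separate a mechanism from shared dependence on age or, in post-baseline data, on arm

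*Protocol article*

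**What the plan says.** The Statistical analysis section names two sets of correlations.

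- Structural MRI: "Pearson correlation analysis will be conducted to assess the relationship between hippocampal subregion atrophy and the volumes of auditory and olfactory regions".
- Connectivity against cognitive and sensory outcomes: "Pearson or Spearman correlation coefficients will be calculated, depending on the distribution of the data".

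The stated purpose follows: "These analyses aim to uncover potential neural mechanisms underlying the effects of the interventions". For neither set does the text name a covariate, an arm term or a time point.

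The structural correlation also has a place among the outcomes. In Objectives and study design, the sentence that begins "Secondary outcomes involve evaluating sensory function through air conduction, pure tone hearing thresholds, and olfactory recognition levels" goes on to include "analyzing the correlation between hippocampal subregion atrophy rates and volumes of auditory and olfactory regions using structural MRI". The hippocampal variable is called an atrophy rate there and simply atrophy in the Statistical analysis section.

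The testing level is fixed: "An alpha level of (0.05) will be considered for all statistical tests", two-sided. Age appears as a design factor only under Intervention program: "the stratification factors considered in this study include sex, years of education, and age".

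**The concern.** A simple coefficient between two participant-level measures contains no treatment term. It answers whether people who are high on one measure are also high on the other. It does not answer whether the intervention moved one through the other.

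Two ordinary routes lead to a non-zero coefficient with no mechanism behind it.

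1. **Age.** Eligibility sets a minimum of 60 years and states no upper limit. Atrophy, regional volumes, hearing, smell and cognition can all be expected to vary with age in such a sample.
2. **Arm.** If post-baseline or change values are used and the interventions move both measures, differences between arm means alone produce a correlation across participants.

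Nothing else described in the plan removes this. Stratifying by age balances age between arms but leaves the age-driven correlation across participants untouched. False discovery rate control deals with the number of tests and takes each p-value as valid.

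At stake are a listed secondary outcome and the mechanistic reading attached to the imaging results. The comparison of arms on cognition is not affected.

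**Working it through.** **Inputs from the protocol article**

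- Sample size section: 36 participants required for imaging, 44 after a 20% dropout allowance.
- Baseline measurement section: at least five participants per arm scanned, so a guaranteed minimum of 5 × 4 = 20.
- Statistical analysis section: two-sided alpha 0.05.
- Objectives and study design: four arms, 1:1:1:1.

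**The plan's own figure.** 36 × 1.20 = 43.2, rounded up to 44, gives the stated number. Dividing instead gives 36 / 0.80 = 45. The 44 is reproduced to within one participant. The base figure of 36 cannot be rebuilt, because the effect size is not in the text. As 44 includes expected dropouts, 36 is the planned analysable number, and it is the main case below.

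**Assumed inputs.** The documents give no correlations with age and no expected arm shifts, so a range is shown.

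**Shared factor such as age.** If two measures correlate a and b with a shared factor and are otherwise unrelated, the population correlation is r = a × b: 0.3 × 0.3 = 0.09; 0.4 × 0.4 = 0.16; 0.5 × 0.5 = 0.25.

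False-positive rates were simulated (40,000 replicates, two-sided 0.05, true partial correlation zero):

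| Correlation of both measures with the factor | Spurious r | n = 20 | n = 36 | n = 44 |
|---|---|---|---|---|
| 0.3 | 0.09 | 6.5% | 8% | 9% |
| 0.4 | 0.16 | 10% | 16% | 18% |
| 0.5 | 0.25 | 19% | 32% | 38% |

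Hand check by Fisher z for r = 0.16, n = 36: atanh(0.16) = 0.161; 0.161 × √33 = 0.927. The upper tail is P(Z > 1.96 − 0.927) = 0.151 and the lower tail is 0.002. The total is about 0.15, against 0.155 simulated.

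**Arm.** Let the combined arm differ from control by d SD on both measures, with the two single-modality arms halfway. The variance of the arm means is v = d²/8, and r = v / (1 + v). For d = 1: v = 0.125 and r = 0.125 / 1.125 = 0.11. Simulated rates with arm ignored:

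| d (SD) | r | n = 20 | n = 36 | n = 44 |
|---|---|---|---|---|
| 0.5 | 0.03 | 5% | 5% | 6% |
| 0.8 | 0.07 | 6% | 7% | 8% |
| 1.0 | 0.11 | 8% | 10% | 11% |
| 1.5 | 0.22 | 16% | 26% | 31% |

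**After adjustment.** With a partial correlation on the shared factor, or on arm, the rate returns to 4.8–5.2% in every scenario and at every n.

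**Cost in precision.** Age uses one degree of freedom and arm three, four in all; intracranial volume makes five. The Fisher-z standard error is 1/√(n − 3 − k) for k covariate terms. Its inflation over the unadjusted coefficient is:

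- n = 44: √(41/37) = 1.05 for four terms, √(41/36) = 1.07 for five;
- n = 36: √(33/29) = 1.07 and √(33/28) = 1.09;
- n = 20: √(17/13) = 1.14 and √(17/12) = 1.19.

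**The case against.** The strongest reply is that a condensed article may leave covariates, analysis set, time point and head-size scaling to the full plan or the imaging pipeline, so their absence proves nothing. That stands as far as it goes. A reader might infer that the four arms will be pooled; the article neither pools nor separates them. What does not depend on silence is that the article names the estimator, gives the rule for choosing between its two forms, and attaches a mechanistic purpose to it.

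Several other limits also stand.

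- **Head size.** A reader might infer that head size drives the structural correlation. If the hippocampal variable is a relative rate, as Objectives and study design suggests, head size largely cancels. It matters only for absolute volumes or absolute losses.
- **Arm.** At baseline, randomisation leaves no systematic arm difference. The artefact needs post-baseline or change values, and for modest effects it is negligible.
- **Importance.** A reader might infer that the hypothesised pathway from sensory function through the brain to cognition rests on these coefficients. The Introduction offers that pathway only as a possibility, the main hypothesis is tested by the mixed model, the connectivity correlations are described as exploring associations, and the Discussion leaves causality to later work. The Abstract and Table 1 do not list the structural correlation as an outcome, although Objectives and study design does.
- **Rates.** The percentages are for single tests at an uncorrected 0.05. With false discovery rate correction the operating rates may differ, but the bias in r stays.

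**Conclusion.** The point holds in a limited form. The method as named is an unadjusted coefficient that cannot carry the mechanistic reading given to it, and the handling of arm and time point is not stated. That much needs no assumed number.

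The size does rest on assumptions. With both measures correlated 0.3 to 0.5 with a shared factor, the false-positive rate is about 8% to 32% at n = 36 (9% to 38% at n = 44; 6.5% to 19% at n = 20). The lower end is not far from nominal. The arm artefact becomes noticeable only at about 1 SD on both measures. Because every input is assumed and the two ranges overlap, the documents do not support ranking age above arm in general, nor a claim that the correlations will be spurious.

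This is a worthwhile, inexpensive improvement to a secondary and mechanistic analysis. It does not threaten the main comparison of arms.

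**What to change.** In the Statistical analysis section, replace the simple coefficients with partial correlations, rank-based where the distribution calls for it, adjusted for age and arm. Add intracranial volume, taken from the structural scan already planned, only where absolute volumes or absolute volume losses are analysed. Keep the adjustment set this small, because as few as 20 participants may be imaged.

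State the time point of each variable. For analyses meant to bear on how the interventions work, correlate changes from baseline in both measures. Report the unadjusted coefficients descriptively, and describe all results as associations rather than mechanisms. If the full analysis plan already adjusts for age and arm, one sentence saying so is enough.

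The change is to wording and uses data the trial already collects. It costs four to five degrees of freedom: the standard error rises by about 5–9% at n = 36 to 44, and by a more noticeable 14–19% if only 20 are imaged. Using changes in both measures also departs from the rate-against-volume pair in Objectives and study design. That pair can stay as an adjusted association, with the change-against-change analysis added beside it.

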### Relevance to government policy

The project aligns with the “14th Five-Year” Healthy Aging of the National Health Commission. The results of this project are of great value to the development of the national old-age cause and the planning of the old-age service system.

## Ethics and dissemination

### Data management

The study will be conducted following Good Clinical Practice (GCP) guidelines. Adherence to two basic principles should be maintained: (1) Data Protection to ensure the anonymity and privacy of our participants; and (2) Data Sharing to ensure that data from publicly funded research are publicly available. We will ensure that all institutional Data Protection requirements are followed. Potentially identifiable personal data will be stored only within secure locations and electronic data in local secure servers, as stipulated within the Personal Data Protection Act 2010 (Ponvel et al., 2021). We would be anonymizing data and enlisting our institutional librarians to assist with data curation before depositing our data in an open data repository within 12 months of project completion.

All physical materials, such as consent forms, completed questionnaires, and demographic details, will be secured in a locked cabinet at the research center at Shanghai University of Sport. Participants will be assigned a numerical code separately to ensure their privacy. Participant names or other identifying features will not appear in data reporting. The coding system will be stored digitally and manually at Soochow University and accessible only to research team members.

### Ethics approval and consent to participate

This study was approved by the Scientific Research Ethics Committee of Shanghai University of Sport on 15 March 2024 (102772023RT200) and approved by the Chinese Clinical Trial Registry on 24 April 2024 (ChiCTR2400083424). All volunteers or their legal representatives will be asked to sign a written informed consent form with prior approval from the ethics committee.

### Discussion

Mild cognitive impairment (MCI) is progressive and affects memory, other cognitive abilities, and motor performance (Jia et al., 2020). These impairments can interfere with an individual’s ability to perform daily activities and are often associated with sensory impairments, which exacerbate cognitive decline (Clemmensen et al., 2020).

Research has shown that sensory disturbances can lead to decreased concentration, increased dependency, and reduced quality of life for patients with MCI (Bouhaben et al., 2024; Deal et al., 2016; Jacobsen et al., 2015). Therefore, early interventions targeting both cognitive function and sensory organ health are essential to maintaining independence and improving quality of life for this population. Tai Chi, a mind-body exercise, has the potential to enhance brain function through its focus on strength, balance, and dual-tasking (Jia et al., 2020; Ponvel et al., 2021). By combining physical movement with controlled breathing and mental focus, Tai Chi promotes both sensory integration and physical adaptation to the environment (Jasim et al., 2023). Sensory function plays a critical role in how the brain processes environmental stimuli, and enhanced sensory input, together with physical activity, may improve functional performance, slow cognitive decline, boost mood, and increase confidence, thereby reducing dependence (Drapeau et al., 2009; Liu et al., 2021; von Bornstadt et al., 2018; Won et al., 2021).

A key strength of this study compared to similar ongoing research is the integration of sensory function into the intervention. While some studies suggest that sensory decline may be associated with cognitive dysfunction, most existing research has focused on patients with Alzheimer’s disease (Jung et al., 2019). This study seeks to extend these findings by investigating the effects of combining motor and sensory interventions on cognitive function in older adults with MCI. Additionally, this study aligns with the World Health Organization (WHO) Global Action Plan for the Public Health Response to Dementia 2017–2025 and the latest Lancet Commission report on dementia prevention and care. It addresses the need for comprehensive data on dementia risk factors and explores innovative approaches to prevention, particularly within culturally and geographically similar environments to China (Ponvel et al., 2021).

This outcome will provide new insights into how sensory and cognitive interact in response to multi-domain interventions. Tai Chi, as a non-invasive intervention exercise practice and one of the traditional Chinese Medicine components, is generally beneficial for recovery of brain cognitive function and rehabilitation and has also been applied extensively in other diseases such as traumatic brain injury (TBI) cases (Zhou, 2020). Multi-domain interventions, such as the one employed in this study, have been suggested as potential strategies to reduce healthcare costs associated with aging populations (Reparaz-Escudero et al., 2024). This study introduces a novel approach by integrating sensory stimulation with Tai Chi to target cognitive and sensory decline in older adults with MCI. Findings are expected to inform public health strategies, contribute to aging policies, and provide a model for scalable, sustainable interventions in similar cultural and demographic contexts.

Future directions for this research could include conducting a detailed correlation analysis between neuropsychological assessments and neuroimaging data. Specifically, investigating the relationship between sensory processing regions and memory-related brain areas, as well as examining the correlation between cognitive scores and specific brain regions, could provide a deeper understanding of the neurobiological mechanisms underlying the observed cognitive improvements. Additionally, longitudinal follow-ups designed to explore causality will be essential in determining whether multi-domain interventions lead to sustained cognitive and sensory enhancements over lasatime.

### Conclusion

This study introduces a novel approach by integrating sensory stimulation with Tai Chi to target cognitive and sensory decline in older adults with MCI. Findings are expected to inform public health strategies, contribute to aging policies, and provide a model for scalable, sustainable interventions in similar cultural and demographic contexts.
